**Methods/design:**

The study applies a two-armed cluster-randomized trial design of a problem-solving intervention conducted in private-sector companies. First-line managers are randomized into intervention- or control groups by computer-generated random numbers, allocation ratio 1:1. Employees are eligible if at risk for future sick leave due to common mental disorders. These are identified by self-reported psychological health measured by the General Health Questionnaire 12-item, cut-off ≥3, or a positive answer to risk of sick leave.

The intervention is based on problem-solving principles. It involves the training of the first-line managers who then deliver the intervention to employees identified at risk of sick leave. First-line managers in the control group receives a lecture. Primary outcome is number of registered days of sick leave due to common mental disorders during the 12-month follow-up. Secondary outcomes are general health, psychological symptoms, work performance, work ability and psychosocial work environment. A process evaluation will examine the intervention’s reach, fidelity, dose delivered, dose received, satisfaction and context. Research assistants managing the screening procedure, outcome assessors and employees are blinded to randomization and allocation.

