### Randomization and blinding

The current study is designed as a two-armed cluster-randomized controlled trial. The randomization of participants is computer-generated, stratified by company, and takes place at the level of first-line managers. They are allocated at the individual level to intervention- or control group by means of computer-generated random numbers with allocation ratio 1:1. The random allocation sequence is generated by an independent statistician. The first-line managers will be enrolled and informed about their allocation by a research assistant.

To avoid contamination, the first-line managers in the intervention arm are instructed to talk and discuss the intervention only with each other and the project team. The first-line managers are not blinded to allocation since they will know about their participation in the problem-solving training (intervention) or the workshop (control condition).

Eligible employees follow the randomization of their first-line manager and are randomized before providing informed consent. All employees, irrespective of whether they are in the intervention- or control group, receive the same information about the study. The information contains details about randomization but not about the content of the two arms, i.e. the employees are blinded for their group allocation. Research assistants, blinded to the first-line managers’ and employees’ randomization, will manage the screening procedure and the outcome assessments (i.e. administration of baseline, follow-up questionnaires and text messages). The statistical analyses will be performed by an independent statistician who will be blinded for the participants’ randomization (both first-line managers and employee).

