### The problem-solving intervention

The intervention is based on a problem-solving technique developed by Nezu et al. [30]. The intervention starts with the training of the first-line managers in the problem-solving intervention by a licensed psychologist (Fig. 2). Thereafter, the first-line managers apply the problem-solving conversation in their meetings with employees at risk of future sick leave due to CMDs. The intervention focuses on the individual employee and his/her work situation and work-private life balance and follows the steps described below. The intervention is carried out between the first-line manager and the employee in 2–5 planned meetings (30–45 min) over a time period of 3 months.

Step 1: Inventory and prioritization of problems by the first-line manager and the employee

In the first step, possible problems related to work are identified and ranked. By establishing a trustful communication, the employee is encouraged to describe his/her work and the background to any problems. The employee’s private life and opportunities for time off work and recovery are examined – if they are relevant to the problem and the employee is willing to share the information. All problems (and opportunities) in relation to work, including possible interference between work and private life, are discussed. A preliminary problem list is compiled and the problems are ranked. Next, the ranked problems are described and defined (including the separation of facts and assumptions, and identification of known barriers) and realistic goals are set. The employee is encouraged to reflect on this prioritization and possible solutions before the next meeting.

Step 2: Brainstorming about options and solutions by the first-line manager and the employee

The purpose of the second step is to brainstorm about as many different options and solutions as possible. These options and solutions are then discussed and evaluated with regard to the following:
will the options and solutions help to solve the defined problem in accordance with the set goals?can the solutions realistically be implemented?what are the advantages and the disadvantages of the brainstormed solutions?what are the short- and long-term consequences for the employee and other stakeholders, such as co-workers, organization?

The employee is encouraged to reflect on the options and solutions before the next meeting.

Step 3: Formulation of an action plan by the first-line manager and the employee

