The aim of third step is to reach an agreement about which solution/−s are to be implemented and to develop an action plan. The plan should describe in detail how the solutions will be implemented; who is responsible for the implementation; when the agreed solutions will be implemented; and when the action plan will be evaluated. At least one solution should preferably start soon after the action plan has been agreed upon and be followed-up shortly. Larger-scale solutions should be divided into several steps. The employee and the first-line manager can, if necessary, involve the human resources department, occupational health services etc. Obstacles and alternative plans should be discussed if the action plan does not work out as intended. The meeting should result in a written action plan, signed by the first-line manager and the employee.

Step 4: Evaluation and follow-up by the first-line manager and the employee

In the fourth step, the action plan is followed-up and evaluated. One to three follow-up sessions (depending on the problem(s)) are recommended, preferably during the first 12 weeks after the last problem-solving meeting, however the number of sessions can be adapted to the employee’s needs. If the action plan has had a positive effect on the defined problem, the follow-up meeting is an opportunity to support and encourage the employee in what has been done. If the action plan did not work or if new problems have occurred, it is an opportunity to discuss the reasons and go back to the problem-solving process or initiate other contacts (occupational health services, human resources department, etc.) if additional support is needed.

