#### Training of the first-line managers in the control group

The first-line managers randomized to the control group will receive a 3-h lecture which includes a brief overview of worker health, work stress and the mismatch model [37]. The information includes protective and risk factors in the work environment in relation to occupational stress and CMDs. Basic information about the importance of self-efficacy for mental health is given, and different ways of interacting with and supporting employees with CMDs are reflected upon. The lecture also includes advice about communication, with focus on general communication skills: listen actively and attentively; encouraging the employee to talk; summarizing and checking your understanding of what has been said; observing and describing the employee’s feelings without judgment [33].

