Previous research indicates that employees with CMDs or mental health symptoms should be given the opportunity to plan and pace their own work [69]. In most cases, support to implement work adjustments from, for example, the first-line manager is needed, because he/she is responsible for leading and allocating the work. In 2015, new provisions about the organizational and social work environment were introduced in Sweden [70]. The new provisions place increased responsibility on the employer to assess physical and psychosocial risks at work and to implement measures to identify, manage and correct potential and real risks. The problem is that first-line management does not always know how to go about this and the provisions do not give guidelines. The problem-solving methodology described in this protocol may be used as a tool for these “corrective measures” with preventive purposes.

The intervention raises ethical issues about personal integrity in relation to employees’ private and working lives and the possible negative consequences of revealing such information to the first-line manager. The employee participating in the current study has the right to choose which matters and/or problems to discuss with the first-line manager and to maintain private life integrity. This is stated in the written information that the employee receives before giving consent to participation. When taking part in the meetings with the first-line manager, the employee is instructed to talk about matters that – from the employee’s perspective - affect his/her work and work tasks. If successful, the problem-solving process may also be applied to the intersection between private life and working life.

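### Employees are described as blinded, but intervention employees can readily infer their arm, so the self-reported secondary and intermediate outcomes cannot be treated as blinded

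*Protocol article*

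**What the plan says.** The abstract (Methods/design) makes the claim without qualification: "Research assistants managing the screening procedure, outcome assessors and employees are blinded to randomization and allocation". The section Randomization and blinding also says that "the employees are blinded for their group allocation", and the only reason it offers is that the information mentions randomisation but leaves out what each arm contains. It adds that employees in both arms receive the same information, and it concedes that managers are not blinded, because they know which training they attended.

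The section on the problem-solving intervention describes what intervention employees go through: "The intervention is carried out between the first-line manager and the employee in 2–5 planned meetings (30–45 min) over a time period of 3 months". The third of its steps ends with a document that they put their name to: "The meeting should result in a written action plan, signed by the first-line manager and the employee". The fourth recommends further follow-up sessions.

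For the other arm, the section on training the control managers says: "The first-line managers randomized to the control group will receive a 3-h lecture". It describes no structured meetings or action plan for control employees.

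On staff, Randomization and blinding states: "The first-line managers will be enrolled and informed about their allocation by a research assistant". The same section, and the text after the employee exclusion criteria, call the research assistants who handle screening and outcome administration blind to allocation.

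**The concern.** Leaving the arms out of an information sheet limits what an employee knows at consent. It does not hide what the employee then receives. Someone who knows the study is randomised, and who then works through a stepwise programme with the manager and signs a plan, has good grounds to infer the arm.

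This matters because the secondary and intermediate outcomes are the employees' own ratings. A reader who takes the blinding statement at face value would treat those results as protected from response bias, and they are not. The exposure is greatest for items that rate the manager, such as quality of leadership and supervisor support, because that manager delivers the intervention. The Strengths and limitations section mentions recall bias and selective response to screening, but not unblinded self-report.

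**Working it through.** The plan attaches no figure to blinding, and the sample size concerns the register outcome, so the check compares statements.

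1. **Ground for the claim.** Employee blinding rests on one thing: the information is identical in both arms and does not describe them. Nothing is said about masking the experience itself, for example by giving control employees meetings of a similar form.

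2. **What each arm's employees experience.** Intervention: from 2 × 30 = 60 minutes to 5 × 45 = 225 minutes of planned meetings over three months, covering ranking of problems, generation of solutions and a signed plan. Control: the lecture goes to the manager. Employees in both arms who screen positive are advised to talk to their manager, so some conversation may occur under control, but no series of steps or signed plan is described.

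3. **The article's own standard.** Managers are called unblinded because they know what they took part in. Employees in the meetings also know what they took part in, so the same reasoning applies to them.

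4. **Who does the assessing.**
   - *Primary outcome:* days of sick leave from employer and MiDAS registers. The employee does not report it.
   - *Secondary outcomes:* general health, anxiety and depression, exhaustion, work stress, work performance, work ability and psychosocial work environment. All come from employee questionnaires or text messages.
   - *Intermediate outcomes:* self-efficacy, influence at work and supervisor support. These are also employee ratings.

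   Randomization and blinding describes the assistants' part in outcome assessment as administering the questionnaires and text messages. The rating is made by the employee, so the assistants' blinding cannot shield it.

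5. **Timing.** Questionnaires fall at baseline, 6 and 12 months; text messages go out every fourth week for 12 months, or 52 / 4 = 13 occasions. Assume the meetings begin soon after baseline, which the article does not fix. Both follow-up questionnaires then come after the three-month meeting period. So do about 10 of the 13 text messages, since about 13 / 4 ≈ 3 fall within it.

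6. **Research assistants.** One sentence has a research assistant tell managers their arm; others say that the assistants who screen and administer outcomes do not know it. Managers are randomised before their employees are screened, and Strengths and limitations relies on assistant blinding to reduce selection bias. The two statements fit together only if different people are meant, and the article does not say so.

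**The case against.** The best defence is that the article says what it means by blinding: identical information without arm content, in a trial where consent follows cluster randomisation. That has real value, because it limits differential consent between arms. It stands as a description of the consent stage, but not as a claim covering follow-up, and the abstract carries no such limit.

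It is also fair to say that unblinded self-report is unavoidable when managers deliver a behavioural intervention, that these outcomes are already secondary or intermediate, and that the article rests its main conclusion on registers. This limits the consequence but does not make the statement accurate.

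Four stronger readings are tempting and are not supported:

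- **That every employee will know the arm.** This is inference. Employees are not told what either arm contains, and control employees may also talk with their manager. The rating of meeting quality in the process evaluation is not stated to be confined to the intervention arm.
- **That the consent information reveals the arm.** The Discussion says of the right to choose what to raise with the manager: "This is stated in the written information that the employee receives before giving consent to participation". Since both arms receive the same information, it cannot by itself show which arm an employee is in.
- **That the screening assistants are unblinded.** The abstract limits the claim to assistants managing the screening, and a different assistant may inform the managers. This is wording to reconcile, not proof of a breach. Inclusion also rests largely on fixed questionnaire cut-offs, which leaves little room for discretion.
- **That who informs the managers affects the self-reports.** It does not. That matter bears on screening and is separate.

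**Conclusion.** The point holds for employees. The protocol claims a property that the design does not provide: intervention employees are not blinded to what they receive and can readily infer their arm. It follows that blinding of outcome assessors cannot be claimed for outcomes that the employee rates. This reaches every secondary and intermediate outcome, with the ratings of the manager's leadership and support most exposed.

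The size and direction of any response bias cannot be derived from the document. A shift in favour of the intervention is plausible but not shown. The conclusion assumes that the intervention is delivered broadly as described and that control employees have no comparable structured programme.

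The register-based primary outcome, its analysis and the sample size are unaffected. One caveat is that a physician's certificate is needed only from day 8, so short absences may still reflect what the employee or manager decides. On the research assistants, the finding is only an unreconciled wording conflict.

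**What to change.** 1. In the abstract and in Randomization and blinding, state that employees are not told the content of the arms before consent but are not blinded to what they receive. Limit the blinding claim to the research assistants who screen and administer outcomes and to the analysing statistician.
2. Add unblinded self-report to the limitations, naming the ratings of the manager. Interpret the questionnaire and text-message outcomes accordingly, with the effectiveness conclusion resting on the register-based primary outcome.
3. State that whoever informs managers of their allocation takes no part in screening or outcome administration. One way is to give the task to the training team, who already know who is in the intervention arm.

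The first two changes are wording only. The third is a clarifying sentence if the roles are already separate, or otherwise one task moved to staff who already know the allocation. No data collection, sample size or analysis changes.

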### The problem-solving intervention

The intervention is based on a problem-solving technique developed by Nezu et al. [30]. The intervention starts with the training of the first-line managers in the problem-solving intervention by a licensed psychologist (Fig. 2). Thereafter, the first-line managers apply the problem-solving conversation in their meetings with employees at risk of future sick leave due to CMDs. The intervention focuses on the individual employee and his/her work situation and work-private life balance and follows the steps described below. The intervention is carried out between the first-line manager and the employee in 2–5 planned meetings (30–45 min) over a time period of 3 months.

Step 1: Inventory and prioritization of problems by the first-line manager and the employee

In the first step, possible problems related to work are identified and ranked. By establishing a trustful communication, the employee is encouraged to describe his/her work and the background to any problems. The employee’s private life and opportunities for time off work and recovery are examined – if they are relevant to the problem and the employee is willing to share the information. All problems (and opportunities) in relation to work, including possible interference between work and private life, are discussed. A preliminary problem list is compiled and the problems are ranked. Next, the ranked problems are described and defined (including the separation of facts and assumptions, and identification of known barriers) and realistic goals are set. The employee is encouraged to reflect on this prioritization and possible solutions before the next meeting.

Step 2: Brainstorming about options and solutions by the first-line manager and the employee

The purpose of the second step is to brainstorm about as many different options and solutions as possible. These options and solutions are then discussed and evaluated with regard to the following:
will the options and solutions help to solve the defined problem in accordance with the set goals?can the solutions realistically be implemented?what are the advantages and the disadvantages of the brainstormed solutions?what are the short- and long-term consequences for the employee and other stakeholders, such as co-workers, organization?

The employee is encouraged to reflect on the options and solutions before the next meeting.

Step 3: Formulation of an action plan by the first-line manager and the employee

The aim of third step is to reach an agreement about which solution/−s are to be implemented and to develop an action plan. The plan should describe in detail how the solutions will be implemented; who is responsible for the implementation; when the agreed solutions will be implemented; and when the action plan will be evaluated. At least one solution should preferably start soon after the action plan has been agreed upon and be followed-up shortly. Larger-scale solutions should be divided into several steps. The employee and the first-line manager can, if necessary, involve the human resources department, occupational health services etc. Obstacles and alternative plans should be discussed if the action plan does not work out as intended. The meeting should result in a written action plan, signed by the first-line manager and the employee.

Step 4: Evaluation and follow-up by the first-line manager and the employee

In the fourth step, the action plan is followed-up and evaluated. One to three follow-up sessions (depending on the problem(s)) are recommended, preferably during the first 12 weeks after the last problem-solving meeting, however the number of sessions can be adapted to the employee’s needs. If the action plan has had a positive effect on the defined problem, the follow-up meeting is an opportunity to support and encourage the employee in what has been done. If the action plan did not work or if new problems have occurred, it is an opportunity to discuss the reasons and go back to the problem-solving process or initiate other contacts (occupational health services, human resources department, etc.) if additional support is needed.

#### Training of first-line managers in the intervention group

The first-line managers take part in a 1 ½ days training course. The training course is provided by a licensed psychologist (BJ) with extensive experience of problem-solving therapy, manager coaching and supervising health care professionals, and the principal investigator ([name]) who also has a thorough knowledge of problem-solving interventions.

The training is based upon interactive and didactic principles, as recommended by Forsetlund et al. [31]. The training includes didactic features (lectures, reading about problem-solving) and participative sessions that provide the opportunity to practice skills (role-play, observations of others role-play, discussions). The first-line managers receive a manual and worksheets for the intervention [14, 32]. In the current project the manual and worksheets have been adapted for use by first-line managers, because they are not expected to have professional training in e.g. communication skills and/or identifying signs of depressive symptoms. The first-line managers will be trained in conversation and communication with focus on: general communication skills, i.e. to listen actively and attentively (use eye contact with the employee, nod, show that you are listening); encouraging the employee to talk and summarize and check your understanding of what has been said; observing and describing the employee’s feelings without judgment [33]. In addition, the first-line managers receive information about validation of communication, which is about communicating an understanding of the other person’s feelings and thoughts [34]. This form of communication does not necessarily mean agreement; it is rather used as a means to acknowledge and legitimize the other person’s experience, which in turn may increase the likelihood that he or she will feel understood. This may result in building trust, reducing emotional intensity and de-escalating possible conflict [35]. We understand some degree of validation to be a beneficial aspect of any type of successful communication, and especially with employees who are at risk of CMDs. These employees may present with some level of emotional vulnerability. Validating communication on the part of the first-line manager may prevent adding further to this vulnerability. If the communication is dis-validating it could confound the effects of the problem-solving. This part of the training is therefore seen as a prerequisite for successful problem-solving.

Between the first and second training sessions, the managers are expected to complete one or two learning assignments. Opportunities and difficulties regarding using the steps of the problem-solving procedure or other aspects of their meetings with the employee are discussed. Common difficulties encountered in the course of the problem-solving intervention, such as defining problems and brainstorming about solutions [36], will be specifically addressed. In addition, the first-line managers are encouraged to use problem-solving whenever possible.

In addition to the training, the first-line managers will be invited to two web-based booster sessions in the first 8 weeks after the training. These sessions include supervision and feedback about the first-line managers’ use of the problem-solving intervention and are based on the first-line managers’ reported cases and/or difficulties. The sessions are led by the licensed psychologist (BJ) and the principal investigator ([name]).

